## Study Outcome Measures

The primary safety assessments will be based on the following outcomes:

• Solicited reactogenicity data acquired from a memory aid that will be kept for Days 0-7 following each product administration by each study participant.

- Local reactions following product administration include erythema (redness), induration (swelling), and pain, tenderness, and/or pruritis (itchiness) at the injection site.
- Systemic reactions following vaccination include feverishness, chills, diarrhea, anorexia (loss of apetite), vomiting, headache, malaise (feeling unwell), myalgia (muscle ache), nausea, rash, arthalgia/arthritis (joint pain/swelling), dyspnea (shortness of breath), wheezing, and abdominal pain.

• Participants will record their oral temperatures daily, as well as any changes that may suggest haematuria or cutaneous abnormalities

• Vital signs and a physical exam including organs targeted in rheumatic fever such as skin, joints, kidney and including cardiac auscultation will be acquired at each study visit.

• Clinical laboratory data acquired at four weeks post-study administration which include haematology, biochemistry, and urinalysis.

The secondary immunogenicity outcomes are based on the following outcomes:

• Production of peptide specific antibodies and increase in the titer for the specific antibodies from the baseline titer after product administration.

- The relationship between the doses administered and the titer of vaccine-specific antibodies

• The percent reduction in a bactericidal assay of group A streptococcus colony forming units (CFU) that elicited vaccine specific antibodies.

- The percent reduction in a bactericidal assay of group A streptococcus CFU achieved in M1, M6 and 88/30 (Australian clinical isolate) group A streptococcus strains

## Study Hypotheses

The hypothesis of this study is that the administration of the vaccine candidate will be safe and immunogenic. This study is not designed to conduct formal hypothesis testing. Only descriptive statistics will be used.

## Participant Enrollment and Follow-Up

Eligible participants will be enrolled from Brisbane, Australia. A follow-up visit will be conducted at Day 180 ± 14 and Day 266 ± 14, which is approximately 12 and 30 weeks respectively following the last injection). The final study visit takes place at day 350 ± 14 (~42 weeks after the last injection). At these visits, vital signs, blood will be collected and targeted physical examinations including cardiac auscultation will be performed. Additionally, the final study visit includes an ECG and ECHO.

The general practitioners (GPs) nominated by the enrolled participants will be informed by a letter that the participants are enrolled in this study and that they may have received a diphtheria toxoid-containing investigational study product. At the completion of the study, another letter will be sent to the participant’s general practitioners describing their participation in the study, including which study product they received, the titer of antibodies for both the vaccine antigen as well as the anti-diphtheria toxoid as measured at the last visit, and any ongoing associated and unassociated adverse events.

## Planned Interim Analyses

### Safety Review

Approximately seven weeks after the first product administration, the Safety Monitoring Committee (SMC) will review study data accumulated up to the five-week time point. The SMC is responsible for monitoring participant safety in this QIMR sponsored study. The SMC will review factors that might compromise the study, such as protocol deviations, and losses to follow-up, and the accumulated safety data.

The data presented to the SMC will not be separated by treatment group. Specifically, data from saline and vaccine candidate recipients will be pooled. SMC members may request additional unblinded analyses at their discretion. The SMC will make recommendations to the Chief Investigator and QIMR as to whether the study should continue, be modified, or terminated, and specifically, whether corrective actions are required, or the study may proceed as planned to the second dose of product.

In the SMC report, the demographics of study participants: age, gender, race and ethnicity; will be tabulated. A table of study completion status will display the counts of participants who are in follow-up, have terminated, or have completed the trial by study group. All subjects dropped from the study will be listed, with the date of termination, length of time on study, and reason for termination. Participant specific protocol deviations will be tabulated according to category and reason for deviation.

Reported safety data will include unsolicited adverse event reports, reactogenicity solicited at one-week post-product administration; hematology, chemistry, and urinalysis at four weeks post-product administration. Additionally, analyses will be conducted with ECG, ECHO at four weeks post-product administration and at the final study visit.

Adverse events will be classified and counts will be expressed in terms of the number and percentage of participants experiencing the event.

Local and systemic reactogenicity will be classified by reaction type, and the maximum grade over the follow-up period for each participant will be reported. The frequency of occurrence and severity of reactogenicity assessments will be summarized in tables and bar-charts.

Summary statistics for clinical laboratory results and vital signs will be calculated by dose number (1 or 2) and time point post-product administration, and will be displayed in both tabular and graphical form. Scatter plots will be used to display individual results by time-point, annotated by summary statistics and laboratory reference ranges. All individual abnormal results will be listed, along with a narrative interpreting the result, if available.

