## Study Outcome Measures

### Primary Outcome Measures

The safety of the vaccine candidate will be assessed on the basis of the frequency and occurrence of injection site and systemic reactions following administration of the investigational vaccine. Adverse events (AE) and serious adverse events (SAE) will be reported throughout the duration of the study. Safety parameters that will be monitored include changes in physical examination including cardiac auscultation, clinical biochemistry and hematology testing on blood and urine, and changes in electrocardiogram or transthoracic echocardiograms.

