Biochemical and hematologic analyses for safety parameters including urinalysis will be performed for all participants at screening, prior to each injection and then at day 28 after each administered dose and at follow-up visits on days 180, 266 and 350. A urine pregnancy test will also be performed for all female participants on the day of each vaccination. Immunogenicity of the vaccine components will be determined by measuring the serum level of GAS peptide specific antibodies and cellular responses on each day of vaccination 28 days after each vaccination and at follow-up visits on days 180, 266 and 350. The induced level of GAS peptide antibodies will be used to monitor the kinetics of the antibody response after two vaccinations and to evaluate the response of subjects receiving the interventional vaccine compared to the placebo saline control. Moreover, serum sample of each participant at time points prior to each injection and at the final study visit on day 350 will be kept for use in testing for presence of human tissue cross-reactive antibodies should suitable assays for detection of cross reactive become available. The level of the anti-diphtheria toxoid antibodies in each participant will be measured prior to the each injection and at the end of the study. The expected duration of participant’s participation from screening to the final follow up visit will be approximately 13 months.

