• Vital signs will be collected and acute complaints examined by clinical personnel prior to each study product administration and at all scheduled clinic visits. Each participant will be subject to a physical examination by a physician at screening to evaluate the general health status of the participant. This will include body weight, vital signs (blood pressure, temperature, heart rate and respiratory rate), an examination of vital organs and cardiac auscultation. Targeted (abbreviated) physical examination including cardiac auscultation will also be performed prior to study product administration of each injection and at all scheduled study visits (Appendix A). Exam will include particular attention to any elicited symptoms and signs consistent with any adverse events. Any deviations from normal will be reported to the study physician for a review. All deviations from normal detected by physical examination will be graded as 1 (mild), 2 (moderate), 3 (severe) and 4 (life threatening) (see Appendix B).

• Transthoracic echocardiography (ECHO) and electrocardiogram (ECG) tests will be performed for each participant in this study at screening, 28 days after each injection and at the final visit on day 350 by a technician blinded to the type of treatment that the participants are receiving. A single echo technician and a single cardiologist have been recruited to perform and interpret all ECHO findings. The technician will be located at the clinical site and the cardiologist reading the findings will be located in the hospital which is physically separated from the clinical site where study activities will be conducted. There will be no discussion regarding the clinical trial between the trial personnel and the hospital personnel. Echocardiograms will be reviewed for any abnormalities by the study cardiologist who will be also blinded to type of treatment that the participants are receiving. If any findings are identified as abnormal a second cardiologist will be asked to independently review the test results and report on the findings. If an abnormal ECHO/ECG is confirmed, it will be reported to the Independent Safety Monitor and Safety Monitoring Committee to determine whether it meets halting rules. Any change in degree of mitral regurgitation with EROA 10-19mm2 but a change of <10mm2 from baseline will be followed on a monthly basis with echocardiogram on a monthly basis until stable (Appendix H).

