### Primary Outcome Measures

The primary objectives of this study are to:

• Evaluate the safety of a Group A Streptococcus vaccine candidate delivered intramuscularly to healthy adults in two doses of 50 μg AcJ8-D adsorbed onto alum.

Safety of the vaccine candidate will be assessed on the basis of the frequency and occurrence of injection site and systemic reactions following administration of the investigational vaccine. Safety parameters include changes in clinical biochemistry and hematology values on blood and urine, and changes in electrocardiogram and transthoracic echocardiograms. Adverse events and serious adverse events will be reported throughout the duration of the study.

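### The laboratory summary for the Safety Monitoring Committee gives post-dose levels only, although the declared laboratory safety parameter is change and pre-dose samples are taken

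*Protocol*

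**What the plan says.** Two sections declare the laboratory safety parameter as change. Section 3.2.1 says: "Safety parameters that will be monitored include changes in physical examination including cardiac auscultation, clinical biochemistry and hematology testing on blood and urine". Section 11.2.1 says: "Safety parameters include changes in clinical biochemistry and hematology values on blood and urine". Both add ECG and echocardiogram. Neither names vital signs.

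The data needed for a change are collected. Section 4 says: "Biochemical and hematologic analyses for safety parameters including urinalysis will be performed for all participants at screening, prior to each injection", and again at Day 28 after each dose. The Day 0 and Day 56 procedures in sections 7.2 and 7.3 list the same blood and urine collection before the injection.

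Section 11.5 lists the laboratory outcome without reference to baseline: "Clinical laboratory data acquired at four weeks post-study administration which include haematology, biochemistry, and urinalysis".

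Section 11.9.1 is the only place that says how laboratory data are summarised: "Summary statistics for clinical laboratory results and vital signs will be calculated by dose number (1 or 2) and time point post-product administration". It adds "Scatter plots will be used to display individual results by time-point, annotated by summary statistics and laboratory reference ranges" and a listing of abnormal results. The same section pools the arms in the SMC report, though members may ask for unblinded analyses.

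Section 11.10.1 does specify change or fold-rise from baseline, but for immunogenicity. It leaves the detail of the final analyses to a statistical analysis plan to be finalised before final database lock.

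**The concern.** The declared parameter is change, and the written summary is a post-dose level. The gap falls in the report on which the SMC decides whether Dose 2 may proceed: the Protocol Summary schedules that review at Day 49, on data up to Day 28.

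Sections 5.2 and 7.1 screen out clinically significant laboratory abnormalities, so most values start within range. A shift after dosing that stays within range would not appear in a listing of abnormal values. In a pooled table of post-dose levels it has no control arm and no pre-dose value to be set against. What is at stake is how easily the committee could see a moderate, systematic laboratory shift before the second dose.

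**Working it through.** **1. No figure to reproduce.** The protocol gives no SD, effect size or within-person correlation for laboratory data. The calculation below is in units of the between-person SD, with rho assumed.

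**2. Which time points the stated summary covers.** It covers post-product time points by dose number. Day 0 is not one of them. The Day 56 pre-dose sample could be read as a late time point after Dose 1, but it falls after the Day 49 review. For the Dose 1 review, then, no pre-dose value enters the stated summary.

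**3. Precision in the pooled SMC report.** Inputs: n = 15 + 5 = 20 (section 11.7, pooled under 11.9.1) and equal variances before and after dosing.
- Mean level: half-width = t(0.975, 19)/√20 = 2.093/4.472 = 0.468 SD.
- Mean paired change: half-width = 0.468 × √(2(1 − rho)).

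| rho (assumed) | √(2(1 − rho)) | Half-width, change (SD) | Half-width, level (SD) |
|---|---|---|---|
| 0.3 | 1.183 | 0.55 | 0.47 |
| 0.5 | 1.000 | 0.47 | 0.47 |
| 0.7 | 0.775 | 0.36 | 0.47 |
| 0.9 | 0.447 | 0.21 | 0.47 |

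A change is estimated more tightly than a level only when rho exceeds 0.5.

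**4. Like-for-like comparison.** A post-dose mean does not estimate a change at all. To obtain one from level tables, a reader would need a pre-dose table and would subtract unpaired means. The standard error of the paired change relative to that difference is √(2(1 − rho))/√2 = √(1 − rho), that is 0.84, 0.71, 0.55 and 0.32 at rho 0.3, 0.5, 0.7 and 0.9. On this comparison pairing helps at any positive rho.

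**5. Dilution by pooling.** A shift confined to vaccinees appears in the pooled mean at 15/20 = 75% of its size. A 0.5 SD shift becomes 0.375 SD. That is inside the change half-width at rho 0.3 and 0.5, about level with it at rho 0.7, and well outside it at rho 0.9.

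**6. The abnormal listing as a substitute.** Assume a normal distribution with the upper reference limit at the 97.5th percentile.
- No shift: the chance that at least one of 15 vaccinees is listed is 1 − 0.975^15 = 0.316.
- 0.5 SD shift: each vaccinee exceeds the limit with probability 1 − Φ(1.96 − 0.5) = 0.072, and the chance of at least one listing is 0.675.

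One listed value is thus common without any shift, and there is still about a one-in-three chance of none when a shift is present.

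**The case against.** The strongest reply is that section 11.9.1 describes an interim report, and that change tables and grade-shift tables are ordinary content of the statistical analysis plan, which is not shown. This stands for the final analysis: nothing in the protocol excludes change analyses there, and tables by arm or for Days 180, 266 and 350 are properly left to that plan. It does not settle the SMC report. Section 11.10.1 defers only the final analyses, to a plan due by final database lock, so that plan need not exist at the Dose 1 review. Here the protocol states a method, and the method does not match its own parameter.

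A reader might infer that shifts are hidden altogether. The documents do not support that. Section 11.9.1 plots individual results by time point, section 11.7 promises a full listing for each participant, section 9.2.1 treats a change from baseline as an adverse event, section 9.2.3 grades laboratory abnormalities, and the committee can ask for more. With 20 people, these routes have value. They are less sensitive to a systematic in-range shift, and none is stated to pair values within person.

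A reader might also extend the mismatch to vital signs. They are measured before dosing (section 8.1: "Vital signs will be collected and acute complaints examined by clinical personnel prior to each study product administration and at all scheduled clinic visits"), but neither section 3.2.1 nor 11.2.1 declares them as change.

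Finally, more intervals mean more chance findings. If 20 analytes were repeated (an illustrative count) with three change intervals each, 60 × 0.05 = 3 would be expected to exclude zero with no true change. That is a reason to label the intervals descriptive, as sections 11.6 and 11.7 already do for all analyses, and not a reason to omit them.

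**Conclusion.** The point holds for laboratory data in the SMC report. Sections 3.2.1 and 11.2.1 declare change, section 4 collects the pre-dose samples, and section 11.9.1 specifies post-dose levels with arms pooled and no pre-dose reference. Section 11.5 repeats the mismatch.

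The statistical gain is real but conditional. Against a mean level at n = 20, a change summary is wider at rho 0.3, equal at 0.5, about a quarter narrower at 0.7 and less than half as wide at 0.9. These figures rest on an assumed rho and equal variances, so no single multiple of sample size can be claimed. The firmer argument does not depend on rho: the stated summary does not estimate the declared parameter.

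This is worth correcting because it bears on the Dose 2 review and the data are already collected. It does not show that the final analysis will lack change tables, nor that the committee would be blind to a shift.

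**What to change.** In section 11.9.1, for each repeated laboratory analyte, add to the SMC report:
- the pre-dose value alongside the post-dose value;
- the paired within-person change, Day 0 to Day 28 for the Dose 1 review, and Day 56 to Day 84 and Day 0 to Day 84 for the Dose 2 review, with mean change and a 95% interval labelled descriptive;
- a table of shift in toxicity grade from pre-dose;
- individual pre/post lines in place of unlinked points.

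Keep the arms pooled for the committee as planned. Reword the laboratory outcome in section 11.5 to match section 11.2.1. Vital signs may be shown the same way as an option. Leave later visits and tables by arm to the statistical analysis plan.

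The cost is wording, a few more tables and figures, and a set of exploratory intervals of which some will exclude zero by chance. No new samples or visits are needed.

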### Immunogenicity Analysis

No interim analyses of immunogenicity are planned.

## Final Analysis Plan

### Immunogenicity Analysis

The ELISA and Indirect Bactericidal Assays will be used to assess the immunogenicity of the vaccine candidate. The standard ELISA will be performed to determine the peptide-specific serum IgG concentrations (μg/mL) in sera of all participants at screening, and at Day 28 after each product administration as well as at days 180 ± 14, 266 ± 14 and 350 ± 14. The Indirect Bactericidal Assay will be used to measure the neutralization abilities of the vaccine-induced antibodies against different standard GAS strains. The percent reduction on GAS colony forming units will be determined.

No interim analyses of immunogenicity are planned. Assay results will be batched and analyzed at the end of the trial. Immunogenicity data will be collected pre-product administration and after each successive dose. All time points will be analyzed, but the focus will be on the immune response at 28 days after the final dose. Parameterizations of immune response will include a) the proportion of participants with a positive response (if criteria for a positive response are developed), b) the mean (or geometric mean) level of the response, c) the change in mean level (or fold-rise) from baseline, and d) the change in mean level (or fold-rise) between successive doses.

A detailed description of the final analyses will be developed in the statistical analysis plan, which will be finalized prior to the final database lock. Any deviations from the plan will be described and justified in the final report.

# Source Documents and Access to Source Data/Documents

Each participating site will maintain appropriate medical and research records for this trial, in compliance with ICH E6 GCP, Section 4.9 and regulatory and institutional requirements for the protection of confidentiality of subjects. Site monitoring is conducted to ensure the human subject protection, study procedures, laboratory, study intervention administration, and data collection processes are of high quality and meet sponsor, GCP/ICH and, when appropriate, regulatory guidelines. Site visits may be conducted by an authorized representative of QIMR or other regulatory agencies to inspect study data, subjects’ medical records, and CRFs in accordance with ICH guidelines, GCP and the respective local and national government regulations and guidelines.

The CI will permit authorized representatives of QIMR and the respective local and national health authorities to inspect facilities and records relevant to this study if needed.

According to ICH GCP, source data correspond to all information in original records and certified copies of original records of clinical findings, observations or other activities in clinical trial necessary for the reconstruction and evaluation of the trial. Source data are contained in source documents and these correspond to ALL original documents, data and records in either hard or electronic format. The source documents include, but not limited to, the hospital records, clinical and office charts, laboratory findings, notes, memoranda, participants diaries or evaluation checklists, pharmacy dispensing records, recorded data from automated instruments, copies or transcriptions certified after verification as being accurate and complete, participant files and records kept in the pharmacy, at the laboratories and other departments involved in the clinical study.

The data will be collected and recorded in the medical record or the source documents first by the CI or the designated clinical personnel and then entered onto the case report form (CRF).

The CI and the clinical personnel involved in the clinical study will ensure that all recorded data are accurate, complete and consistent as in accordance with the ICH GCP requirements and the site specific protocol for completion of documentation. The clinical staff involved in the study will also ensure that all records for receipt, shipment and other disposition of the study products are maintained, complete and accurate during the clinical study.

The CI is responsible to ensure that all data reported on the CRF and derived from the source documents are consistent and any discrepancies explained. To protect the confidentiality of the participants, the accuracy and the completeness of the study records only the CI and the study personnel designated by the CI will be granted an access and authorization to enter additional data to the source data. The CI will ensure that the designated study personnel are qualified appropriately and familiar with the ICH GCP requirements for conductance of clinical trial.

Upon request, the CI will permit direct access to source data/documents for trial related monitoring, audit, HREC review and regulatory inspection(s) by the sponsor or their appropriately qualified delegate and inspections by TGA. Direct access includes examination, analysis, verification and reproduction of records and reports that are important to the evaluation of the trial.

Forms for use as source documents will be derived from the CRFs.

